# Introduction

Dry eye disease (DED) is an emerging, under-recognized and under-treated epidemic of the 21st century. It is one of the commonest reasons seeking eye consultation worldwide. Depending on the diagnostic criteria, geographic location and population concerned, prevalence of DED ranges from 30 to over 50% in the Asia Pacific regions compared to around 5-10% in the United States [1-2]. Up to 90% of DED is closely associated with meibomian gland dysfunction (MGD),[3] a chronic and progressive condition characterized by terminal duct obstruction, qualitative and/or quantitative changes in the glandular secretions (meibum) which causes tear instability by increasing tear evaporation and subsequently increased tear osmolarity, ocular surface inflammation, epithelial damage and ocular surface disease. Studies suggest that MGD affects between 5-20 % of Caucasians and over 60% of Asians populations.[4-5]

Conventional treatments for MGD including self-administered eyelid hygiene, eyelid warm compress therapy (EW), artificial tears, including lipid‐containing lubricants are limited in their efficacies for moderate to advanced disease.[6] Prescription medications (topical steroids, topical and oral antibiotics, topical immunomodulatory agents e.g. cyclosporine and oral omega-3 essential fatty acids) have demonstrated efficacies in improving symptoms and signs of MGD;[7-8] however side-effects including preservative-related adverse events, development of antibiotic resistance, cost, accessibility, off‐label use, and the need for ongoing treatments often limit their long‐term use.[9-10]

Despite the described range of available options, management for MGDs is often considered unsatisfactory and frustrating by clinicians and patients. Compliance to long-term, home‐based self-administered therapies is known to be suboptimal [8-10] while practitioner-administered treatment including meibomian gland expression (MGX) provides transient relief.[11-12]

Intense pulsed light (IPL) therapy is widely used in cosmetic dermatology as well as therapeutically for a wide range of skin conditions with favourable efficacy and tolerability. Concurrent MGD improvements were observed serendipitously in patients undergoing IPL for rosacea.[13] With growing interest in combining IPL+MGX as practitioner-administered physical therapy for MGD, recent review and meta-analysis showed its effectiveness and safety while calling to investigate its effect beyond 6 months after the last IPL treatment [14-16].

Vectored thermal pulsation (VTP) is approved by FDA as another practitioner-administered physical therapy for MGD. The device covers both the cutaneous and mucosal surfaces of the eyelids; the rear portion of the device provides heat to the MG, and the front portion gives mechanical stimulation to the eyelid skin. It evacuates the MG of the upper and lower eyelids simultaneously with minimal discomfort while protecting the cornea, rendering the experience for patients generally favorable. Recent meta-analysis showed that a single 12-minute VTP was more efficacious than EW in treating MGD [17].

Knowledge gaps

Level I evidence comparing efficacies between two promising practitioner-administered therapies VTP and multi-session IPL+MGX with standard self-administered twice-daily EW for MGD is currently lacking. The onset and offset of therapeutic effects, time course of multi-session IPL+MGX, single-session VTP or twice-daily EW on MGD up to 15-month post-treatment initiation or 12-month post last session of IPL have not been studied either in an RCT setting. These important gaps will be addressed in this application.

# Aims and hypotheses to be tested

Primary Objective

To compare the efficacy and safety of 1-session vectored thermal pulsation (VTP) or 4-session intense pulsed light and meibomian gland expression (IPL+MGX) with twice-daily eyelid warm compress (EW) therapy for meibomian gland dysfunction (MGD)

Secondary Objectives

1. To compare the course of MGD among groups over 15 months (12-month after final IPL+MGX)
2. To identify factors predicting responses and compliance to therapies

Hypotheses

1. Both 1-session VTP and 4-session IPL+MGX are more efficacious than twice-daily EW in improving MGD
2. MGD improves earlier after VTP
3. MGD improvement lasts longer after 4-session IPL+MGX

# Plan of investigation

## Subjects

A total of 360 patients with symptomatic MGD will be recruited from the participating hospitals coordinated by the Chinese University of Hong Kong (CUHK) Research Clinic, the CUHK Eye Centre (CUHKEC), Department of Ophthalmology and Visual Science, Faculty of Medicine, The CUHK. Open recruitment will be made possible by the use of online channels, as well as promotional flyers and QR codes to be distributed at the participating hospitals. We adopt some of the inclusion and exclusion criteria of recent RCT on MGD [18-19].

Inclusion criteria include:

1. ≥18 years of age with no upper age limit;
2. Providing informed consent, agree to attend follow-up visits and comply to treatment regimen
3. Symptomatic dry eye TFBUT ≤ 5 seconds and OSDI ≥ 13[20];
4. Mild to moderate (level 3-4) MGD on at least one eye[21];
5. Fitzpatrick skin type 1-4.

Exclusion criteria are:

1. Contact lens wear 3 months before or during the study period;
2. Use of topical (including anti-glaucomatous, cyclosporin, antibiotics) or systemic medication known to affect (worsen or improve) MGD 3 months before or during the study period;
3. Major systemic (e.g. Sjogren’s syndrome), dermatologic (e.g. Rosacea) known to affect MGD or ocular conditions (including thyroid eye disease, recurrent conjunctivitis, ocular allergies);
4. Ocular procedures (excluding uncomplicated cataract operation) 3 months before and any ocular procedure during the study period;
5. History of vision correction surgery or plan to undergo the procedure during the study period;
6. Dermatological treatment (including chemical peeling, laser, IPL or energy device in the periocular and facial region) 6 months before or during the study period;
7. Contraindications to IPL therapy (including recent sun-burn, photosensitivity, active or pigmented skin lesions, cancer, implants, tattoos, semi-permanent makeup in the periocular area);
8. Contraindications to VTP therapy (ocular surgery, ocular injury, ocular herpes of eye or eyelid, and ocular inflammation 3 months before the study; active ocular infection, etc.);
9. Women who are pregnant, nursing, planning pregnancy, or of childbearing potential not using a reliable method of contraception.

## Methods

All measurements are conducted in accordance with the recommendations of the TFOS DEWS II Diagnostic Methodology subcommittee [22].

Participants will be assessed in a designated room at CUHK Eye Centre or CUHK Medical Centre Eye Centre with temperature of 20.3±0.5°C and relative humidity of 63±7% by the same study personnel (research assistants) masked to the treatment assignment. To minimise the impact on subsequent tests, measurements are performed in ascending order of invasiveness and are summarised in Table. The following will be measured or conducted before each treatment or follow-up visit.

Questionnaires (Traditional Chinese version)

Demographic and baseline characteristics, chronic condition, eye disease, surgery & hospitalization history, smoking & alcohol use history, life conditions, and work productivity, etc., are collected via standard questionnaires when subjects are recruited. The 12-item symptom frequency-based questionnaire Ocular Surface Disease Index **(OSDI)**, Standard Patient Evaluation of Eye Dryness **(SPEED)**, 2-item frequency- and severity-based visual analog scale Symptom Assessment iN Dry Eye **(SANDE)**, Ocular comfort index **(OCI),** and Dry eye questionnaire **(DEQ-5)** are self-administered at each study visit.

Visual acuity

Visual acuity of the participant is examined by a standard visual acuity chart as safety outcome measures.

Intraocular pressure

The intraocular pressure, the fluid pressure of the eye, is assessed by a non-contact tonometer as the safety outcome measure.

Keratograph 5M (Oculus, Wetzlar, Germany)

**Non-invasive keratograph break-up time (NIKBUT)** is measured using automated detection of first break-up, while the subject maintains fixation and is requested to refrain from blinking. Three breakup time readings are averaged in each case.

**Bulbar conjunctival hyperaemia** is evaluated according to the proprietary JENVIS grading scale from 0 to 4.

The lower **tear meniscus height (TMH)** is assessed using high magnification pre-calibrated digital imaging, and three measurements near the centre of the lower meniscus are averaged.

Lipiview II

**Lipid layer thickness (LLT)** of the tear film as determined with LipiView II (TearScience, Morrisville, NC).

**Tear interferometric fringe pattern** is graded according to the modified Guillon-Keeler system: grade 1, open meshwork; grade 2, closed meshwork; grade 3, wave or flow; grade 4, amorphous; grade 5, colored fringes; grade 0, non-continuous layer (non-visible or abnormal colored fringes).

**Infrared meibography** is taken with the superior and inferior eyelids everted in turn. From the captured image, the proportion of meibomian glands visible within the tarsal area is graded according to the four-point meiboscore (0-3) by Arita et al. Morphological changes of meibomian glands is assessed by the ‘meibograde’ method evaluating gland distortion, gland shortening and gland dropout. Each of these characteristics is graded from 0-3, like the meiboscore, and then they are summed to give a total score of 0-9 per eyelid where a higher score represents a higher percentage of gland loss.[25]

**Partial blinking** is reported as % recorded by the Lipiview II.

Schirmer’s test (ST)

**Schirmer’s test (ST)** will be performed without anesthesia for 5 mins. The strips will be collected in sterile centrifuge tubes respectively for laboratory tests of biomarkers.

Slit-lamp biomicroscopy (to be performed by masked follow-up investigators)

**Lid margin and eyelash abnormalities**, including lid margin thickening, rounding, notching, foaming, telangiectasia, meibomian gland capping, staphylococcal lash crusting, seborrheic lash crusting, Demodex lash cylindrical collarettes, madarosis, poliosis, and trichiasis, are graded based on a four-point scale: grade 0, absent; grade 1, mild; grade 2, moderate; grade 3, severe.

Sodium fluorescein dyes are applied using the recommended technique described [21].

**Tear film break-up time (TFBUT)**, defined as the time to initial breakup of the tear film after a blink is measured three times.

**Corneal and conjunctival staining** score due to epithelial desiccation is documented according to the modified Oxford grading scheme.

**Lid wiper epitheliopathy (LWE)** is evaluated relative to Korb’s grading.

**Expressibility** of the inferior eyelid meibomian glands is assessed with the Meibomian Gland Evaluator (TearScience, North Carolina, USA) applied just inferior to the nasal, central, and temporal aspects of the eyelid margin. The proportion of meibomian orifices yielding lipid secretions is graded on a five-point scale: 0, more than 75%; 1, 50% to 75%; 2, 25% to 50%; 3, less than 25%; 4, none.

The meibomian glands yielding liquid secretion (MGYLS) is the total number of glands which yielding lipid secretions at the nasal, central, and temporal aspects of the eyelid margin (5 glands each part).

**Quality of expressed meibum** is graded on a four-point scale: grade 0, no secretion; grade 1, inspissated (semi-solid, toothpaste-like consistency); grade 2, colored/ cloudy liquid; grade 3, clear liquid oil. The sum scores of 15 glands will be between 0 and 45.

Dilated fundus examination, anterior chamber activities, lens opacity based on lens opacities classification system II (LOCS II), and iris defect/transillumination will be conducted as safety outcomes.

Conjunctival swab sampling

Sterile, polyester swabs will be applied for conjunctival swab sampling on the inferior fornix of the conjunctiva in each eye. The swabs will be placed in microcentrifuge tubes. Extraction will be performed by laboratory staff, then the sample will be transferred to a -80 °C laboratory freezer for long-term storage before laboratory tests.

Blood specimens collection

Participant's blood specimens will be collected at the baseline visit and pre-treated for further laboratory tests. After genomic DNA extraction from venous blood, Single-nucleotide polymorphism (SNP) will be selected, sequenced and compared between treatment groups for pharmacogenomic analyses.

Expressed meibum sampling

Sterile, polyester swabs will be applied for collection of expressed meibum on the nasal, central, and temporal aspects of the eyelid margin in each eye during the examination of expressibility and quality of expressed meibum.

The expressed meibum by compression forceps after MGX treatment procedure will be collected among the IPL+MGX group subjects.

The swabs will be placed in microcentrifuge tubes. Extraction will be performed by laboratory staff, then the sample will be transferred to a -80 °C laboratory freezer for long-term storage before laboratory tests.

Vectored thermal pulsation (VTP) therapy

VTP (LipiFlow® Thermal Pulsation System, Johnson & Johnson, USA) is an automated thermal pulsation system that is designed to heat and simultaneously evacuate the meibomian gland contents. It is performed by the unmasked treating investigators as described by the equipment manufacturer. In brief, one to two drops of topical anesthesia are applied prior to the bilateral application of the activators. The inner portion of the activator applies a constant temperature of 42.5°C to the tarsal conjunctiva of upper and lower eyelids. Simultaneously, the outer portion of the activator applies directional, pulsatile pressure to the external eyelid surfaces (maximum 6 psi) for the 12-minute treatment cycle. Subjects will feel warmth and pressure on their eyelids during the 12-minute bilateral procedure. All subjects are examined at the slit lamp after the procedure. A procedure related pain score by Visual Analogue Scale (VAS) is obtained by the treating investigator immediately.

Intense pulsed light with meibomian gland expression (IPL+MGX) therapy

IPL is delivered using the proprietary “dry eye mode” setting of the Lumenis® M22TM system (skin type settings 1–4 and mode A–F) per the Toyos protocol (13). Pulse intensity (11-14 J/cm2) is inversely related to the Fitzpatrick skin phototype of each participant and will be used for the same patient throughout the study. Adjustment is allowed due to safety (e.g. treatment related pain) and will be recorded. Clear conducting gel will be applied to the inferior, lateral, and medial aspects of the goggles, as per manufacturer recommendations. IPL will be delivered to four overlapping zones inferior to each eye and a fifth pulse applied temporally adjacent to the lateral canthus four times (month 0,1,2,3). Both eyelids are closed and sealed with IPL-Aid disposable eye shields (Honeywell Safety Products, Smithfield, RI). Safety goggles are worn by the unmasked treating investigators and trial coordinator present during IPL. Meibomian gland expression is immediately performed on both upper and lower eyelids of each eye and pain will be minimized by topical anesthetic. A procedure related pain score by VAS is obtained by the treating investigator immediately. Visual acuity, slit lamp examination to record any iris injury, change in lens opacity by LOCSIII, and external examination on periocular skin, eye lash and eyebrow hair injuries before and after IPL and at each study visit. Each session of IPL and MGX takes about 20 minutes.

Both VTP and IPL therapies are not available and have not been adopted in public hospitals under the Hospital Authority.

Eyelid Warm Compress Therapy (EW)

EW using warm wet towel to each eye is performed twice daily for 10 mins [9-11]. A treatment diary will be given for patients randomized to EW for daily recording which will be reviewed and recorded by the unmasked study coordinator at each study visit.

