Randomization will be carried out by a computer-generated minimization program. Minimization is a dynamic process to reduce the imbalance between trial arms with respect to a range of predefined prognostic variables, and a randomisation schedule is therefore not drawn up in advance. A form describing the baseline characteristics of each subject according to these minimisation criteria: gender (female, male), age (<45, >45), worst meiboscore (0 vs 1 vs 2 vs 3) from the study eye (lower lid) and referring centres will be filled at recruitment (month-1), returned to Centre for Clinical Research & Biostatistics, CUHK on enrolment. Treatment allocation will be sent to the unmasked trial coordinator for arrangement at baseline (month 0).

IPL or VTP is given by **unmasked treating investigators** not involved in data collection.

**Follow-up investigators** collecting the data are masked to participants’ treatment assignment. This information can be disclosed upon request after the completion of the study.

**Unmasked trial coordinator** will ensure masking by reminding and accompanying each patient before and during visit. Treatment related complications will be evaluated by all participants in a standard datasheet regardless of group assignment. Follow-up investigators will be asked if they know each participant’s group assignment at each visit and why.

Escape rule/withdrawal

Subjects recruited from HA can withdraw their consents at any stage but will be invited to continue follow-up at CUHKEC. They will be managed as per standard of care by referring ophthalmologist. Subject will leave study protocol and be terminated from the study but will be followed and assessed as a study patient if they develop any of the following complications:

1. microbial or marginal keratitis
2. Serious Adverse Event (SAE) potentially attributable to VTP or IPL+MGX

Subjects who develop worsening/progression of their MGD will be managed as per medical standard by their referring ophthalmologist by topical/systemic antibiotics, meibomian gland expression which will be documented as protocol deviation.

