## Data processing and analysis

Trial biostatistician will oversee data acquisition, processing and statistical analysis.

Record keeping, confidentiality and monitoring

A unique study number will be assigned to each recruited subject for all study-related documents. The log containing study number to identifiable information will be kept in a locked cabin at the clinical trial office at CUHKEC. All trial-related documents will be maintained by the unmasked trial coordinator to ensure data are accurate, complete, and verifiable from case report forms. Data entry will be cross-checked by a designated technician.

**Primary outcome**: Tear film breakup time (TFBUT) at month 6, month 15

**Secondary outcomes**: Serial measurements of MG, tear-film related parameters, intraocular pressure, compliance to EW, factors associated with MGD outcomes and treatment related complications.

Sample size calculation

Based on Arita et al for IPL+MGX[23] and Lane et al for VTP[24], the estimate mean differences in changes of TFBUT are 3.3 for IPL+MGX and 1.9 for VTP, the pool estimates of SDs are 1.88 for IPL+MGX and 4.04 for VTP. Given a 2.5% type I error (Bonferroni correction) and assuming an average SD of 3, a minimum sample of 88 patients per group can detect a significance difference in change of TFBUT between groups. By assuming a 35% of drop-out over an extended study period (16 months from recruitment), 120 subjects per group are required. This sample size is powered to detect differences between VTP and EW or between IPL and EW given the estimates of EW from Lane et al.

Statistical analysis

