The intention-to-treat principle will be applied during the data analysis using Graph Pad Prism version 8.01 (California, USA) and IBM SPSS version 24 (New York, USA) and reported according to CONSORT guidelines for RCT. Categorical data at baseline are analysed using chi-squared or Fisher’s exact tests. Data are presented as mean± SD, or median (IQR) unless otherwise stated. Study outcomes will be compared between groups using pair-wise t-test. Continuity-adjusted chi-squared testing will be applied to compare proportion of patients between treatment arms on secondary outcome. Further comparisons of the primary and secondary outcomes between treatment arms, at baseline and pre-set intervals will be made using risk ratio (RR) for dichotomous data and mean difference for continuous data with 95% confidence interval. Appropriate (logistic or linear) regression models, adjusting for minimisation and outcome variables at baseline will be computed for prognostic factors. Multivariate analyses will be conducted to control with baseline measurements, covariates, and repeated measurements. Correlations between parametric and nonparametric data are assessed with Pearson product-moment correlation or Spearman rank order correlation, respectively. The proportions of eyes developing complications during and after the procedures are compared with Chi-square test. All tests are two-tailed, and p<0.05 is considered significant.

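### Comparing SNPs between the randomised groups tests only chance imbalance in genotype and cannot yield a pharmacogenomic finding

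*Protocol*

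**What the plan says.** Under Methods, Blood specimens collection, the protocol states that "blood specimens will be collected at the baseline visit". The Study Table agrees: the blood row is crossed out at every visit from month 1 to month 15. After DNA extraction, "Single-nucleotide polymorphism (SNP) will be selected, sequenced and compared between treatment groups for pharmacogenomic analyses". The sentence names a variable (SNP) and a contrast (treatment groups). It names no outcome and no definition of response.

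Under Study design, "Randomization will be carried out by a computer-generated minimization program". The minimisation factors are gender, age group, lower-lid meiboscore of the study eye and referring centre. Genotype is not among them.

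Three other places bear on prediction of response:

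- Secondary objective 2 is "To identify factors predicting responses and compliance to therapies".
- The secondary outcomes include "factors associated with MGD outcomes and treatment related complications".
- The Statistical analysis section says: "Appropriate (logistic or linear) regression models, adjusting for minimisation and outcome variables at baseline will be computed for prognostic factors".

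None of the three mentions SNPs. The Statistical analysis section also sets two-sided p<0.05 for all tests, and chi-squared or Fisher's exact tests for categorical baseline data.

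**The concern.** A pharmacogenomic question asks whether people with different genotypes respond differently, and whether that difference depends on the therapy. It needs an outcome. The stated contrast has none: it asks whether the arms differ in genotype. Since allocation does not depend on genotype, the arms can differ only by chance, so the analysis amounts to a baseline balance check.

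Two things are at stake. First, the only genetic analysis that the protocol describes carries no information about who benefits from VTP, IPL+MGX or EW, although participants give blood for it. Second, at p<0.05 some SNPs will probably appear to differ between arms if many are tested, and such a difference could be reported as a pharmacogenomic result when it is a false positive.

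**Working it through.** The protocol gives no figure for the genetic analysis (no number of SNPs, allele frequency or power), so there is none to reproduce. The check is one of logic, with a simulation and a simple count as illustration.

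**Step 1: the null is true by design.** Let G be genotype and A the arm. G is fixed before allocation and unaffected by A. Allocation uses gender, age, meiboscore, centre and chance, not G. Hence the distribution of G is the same in all three arms, and a valid test of G against A rejects with probability of about 0.05. The effect of G on TFBUT does not enter this statement. If a SNP is associated with a minimisation factor, minimisation would tend to improve its balance, not worsen it.

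**Step 2: simulation.**

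- From the protocol (Sample size calculation): SD of TFBUT change 3; 120 per arm, or 120 × (1 − 0.35) = 78 per arm after the assumed 35% drop-out; a mean gain of 1.9 s, applied to both active arms. Arm main effects drop out of both tests.
- Assumed, not in the protocol: minor allele frequency 0.2, 0.3 or 0.4; an extra TFBUT gain of 0, 1 or 2 s per allele in one active arm only; genotype drawn independently of arm.
- 4,000 trials for each of 18 settings, two-sided alpha 0.05.

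Share of trials that reject (range over the three allele frequencies):

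| Per arm | True effect per allele | Genotype by arm (as stated) | Genotype × arm interaction on TFBUT change |
|---|---|---|---|
| 120 | 0 s | 4.3%–5.0% | 5.0%–5.2% |
| 120 | 1 s | 5.0%–5.7% | 30%–44% |
| 120 | 2 s | 4.8%–5.4% | 84%–96% |
| 78 | 0 s | 4.7%–5.2% | 4.6%–5.5% |
| 78 | 1 s | 4.5%–4.7% | 22%–30% |
| 78 | 2 s | 5.1%–5.5% | 67%–83% |

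The Monte Carlo standard error at 5% is √(0.05 × 0.95 / 4000) = 0.34 percentage points, so the spread of 4.3% to 5.7% in the stated test is simulation noise around 5%. That test does not react to the genotype effect. The interaction test does. Its powers are for a single SNP without multiplicity correction.

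**Step 3: expected false signals.** With m SNPs and k tests per SNP, the expected count is m × k × 0.05. Correlation between the tests does not change an expectation.

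| SNPs (assumed) | One three-arm test (k = 1) | All three arm pairs (k = 3) |
|---|---|---|
| 5 | 0.25 | 0.75 |
| 20 | 1 | 3 |
| 100 | 5 | 15 |

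The column k = 1 is closer to the plan's rule for categorical baseline data. The pair-wise t-test in the Statistical analysis section is attached to study outcomes, not to genotype.

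**The case against.** The best defence is that the sentence sits among instructions for handling specimens, names no test, and gives a pharmacogenomic purpose. On a generous reading it means that associations between SNPs and response will be compared across arms. That may be the intention, but it is not what the words say: the SNPs themselves are what is compared, and no outcome is mentioned. An analysis plan that related genotype to response would replace this sentence, so the sentence needs correcting either way.

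Other parts of the defence stand and limit the point:

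- A reader might infer that secondary objective 2 fails. The protocol does not support that. The objective promises no genetic answer, its non-genetic predictors can be studied through the planned regressions, and nothing in the Statistical analysis section bars SNPs as covariates.
- A reader might fault the prognostic regression for lacking a treatment interaction. Model terms, SNP selection and multiplicity rules are commonly left to a statistical analysis plan, which is not at hand, so their absence is no error.
- A reader might quote three false signals as the size of the problem. That figure needs 20 SNPs and all arm pairs, and the protocol states neither.

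It is also fair to say that the replacement has limited power: 22% to 30% at 78 per arm for an effect of 1 s per allele, before any multiplicity correction.

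Lastly, the flow chart shows randomisation at month −1 while blood is drawn at month 0. Differential loss in between could create a genotype difference that is not pure chance, but it would still say nothing about response.

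**Conclusion.** The point holds for the comparison as stated. A genotype-by-arm comparison is uninformative about response, because its null hypothesis is true by allocation and its rejection rate stays at about 5% per test. This conclusion rests on genotype being fixed before allocation and allocation being independent of it, not on the assumed allele frequencies or effect sizes. The false-signal counts and the interaction powers do depend on such assumptions and serve only as illustrations.

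The fault is a wrong stated contrast in one sentence. The documents do not show that no response analysis will be done. The primary TFBUT comparison is untouched, and the DNA and outcome data needed for a valid analysis are collected anyway. It should be corrected, but it does not threaten the trial's main conclusions.

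**What to change.** In Methods, Blood specimens collection, replace the between-group comparison of SNPs with an exploratory analysis of genotype and response. Suggested content: for each selected SNP, TFBUT at month 6 and at month 15 is regressed on genotype, arm, genotype × arm, baseline TFBUT and the minimisation factors (gender, age group, meiboscore, centre). The genotype × arm term addresses whether the effect of genotype differs by therapy. State that the analysis is exploratory, that multiplicity is controlled across SNPs (for example by the false discovery rate), and that power for modest interactions is limited. If genotype frequencies by arm are shown at all, present them as baseline description without a pharmacogenomic interpretation.

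The cost is one or two sentences and a different model on data already planned. It needs no extra visit, sample or participant. The SNP list and model details can go into the statistical analysis plan.
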